#### Documentation of AEs

All AEs reported by the subject or detected by the investigator will be documented on the appropriate pages of the case report form (CRF). AEs must also be documented in the subject’s medical records.

The following approach will be taken for documentation:

- All adverse events (whether serious or non-serious) must be documented on the “Adverse Event” page of the CRF.
- If the adverse event is serious (see Section 6.2.1.1), the investigator must complete, in addition to the “Adverse Event” page, a “Serious Adverse Event” form in the CRF at the time the serious adverse event is detected.

Every attempt should be made to describe the adverse event in terms of a diagnosis. If a clear diagnosis has been made, individual signs and symptoms will not be recorded unless they represent atypical or extreme manifestations of the diagnosis, in which case they should be reported as separate events. If a clear diagnosis cannot be established, each sign and symptom must be recorded individually.

All questions on the completion and supply of adverse event report forms and any further forms issued to the investigator at a later date to clarify unresolved issues should be addressed to the sponsor.

#### Immediate reporting by investigator

SAEs must be reported immediately within 24 hours after the SAE becomes known via facsimile using the "Serious Adverse Event" form to:

| IZKS Mainz  [name]  [contact] |
| --- |

The initial SAE Report must be as complete as possible including details of subject’s identification (screening number, random number), the (serious) adverse event (medical term, diagnosis), the trial medication and an assessment of the causal relationship between the event and the trial medication made by the investigator.

The investigator should provide related additional information on the clinical course and the outcome of each SAE as soon as possible via facsimile to IZKS Mainz using the SAE form (Follow up report).

The “Serious Adverse Event” forms are provided in the Investigator Site File.

The investigator must also inform the trial monitor in all cases. The sponsor will ensure that all legal reporting requirements are met.

In addition, any pregnancy diagnosed in a female subject or in the female partner of a male subject during treatment with the investigational product must be reported to the sponsor immediately via facsimile using the SAE form.

Worsening of a sign or symptom of the condition under treatment will normally be measured by efficacy parameters. However, if the outcome fulfils the definition of “serious adverse event”, it must be reported as such.

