### Withdrawal criteria

Subjects can be withdrawn their consent at their own request without given reasons at all time during the trial. This should be without disadvantages for the subject. However the investigator should try to perform a final visit to get concluding findings of investigation.

Subjects may be withdrawn from the trial for the following reasons:

- At their own request or at request of the legal representative.
- If, in the investigator’s opinion, continuation of the trial would be detrimental to the subject’s well-being.
- For women, if it becomes known that the subject is pregnant before Visit 2.
- Therapy with oral acetazolamide will be stopped if one or more of the following symptoms occur: allergic reactions (exanthema, relevant changes in blood count), renal colics, visual impairment, prolonged loss of appetite, vomiting, permanent paresthesia and /or centralnervous dysfunction (dizziness, ataxia, amentia).

The Principal investigator decides about withdrawal of subjects from the clinical trial in case of occurrence of criteria mentioned above.

In all cases, the reason for withdrawal must be recorded in the CRF and in the subject’s medical records. In case of withdrawal of a subject at his/her own request, as far as possible the reason should be asked for and documented. The subject must be followed up and as far as possible; all examinations scheduled for the final trial day should be performed and documented.

All ongoing serious adverse events of withdrawn subjects have to be followed up until no more signs and symptoms are verifiable or the health condition of the subject has stabilized, but no longer than 30 days after subjects discontinuation from the trial.

Withdrawn subjects will not be replaced.

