# TRIAL Treatments

## Investigational treatments

**Test product:**

28 days preoperatively (± 3 days): Discontinuation of all local antiglaucomatous drugs and IOP regulation with COSOPT-S® (dorzolamide 20mg/ml and timolol 5mg/ml, MSD) eye drops b.i.d. (7:00 am, 7:00 pm; +/- 1 h)

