**Reference therapy:**

Preoperative standard management of the Department of Ophthalmology, University Medical Center Mainz:

28 days preoperatively (± 3 days): Discontinuation of all local antiglaucomatous drugs and IOP regulation with oral acetazolamide 250 mg - 1500mg per day (two or three doses, dosis depending on IOP); potassium monitoring and potassium replacement if required.

7 days preoperatively (±1 day): Preservative-free dexamethasone 1mg/ml eye drops five times per day

All patients will be assigned to receive either test product or reference therapy formulations as per the randomization schedule. Both treatment phases have duration of four weeks. Treatment with study medication will be discontinued at the end of the study. The investigator will give the total quantity for the treatment phase of the investigational product to the eligible subject at visit 1. At the inclusion visit, each subject will be explained in detail the mode of administration of the test product and reference therapy, as well as a follow-up notebook in which the subject should report any deviations from the stipulated frequency of application, any problems of local tolerability, any adverse reactions, and any comments related to the study that he/she may wish to add.

If the subject is unable to read, the legally acceptable representative, according to the subject’s opinion, should fill in the follow-up notebook. At the last visit, all the investigational medicinal products (full, half-used or empty) must be returned to the investigator. If the products are not returned, the investigator will question the subject to determine the reason for this.

At each visit, any change in the frequency of administration of the test product will be recorded in the Case Report Form. This evaluation will be based, in particular, on the data recorded in the follow-up notebook given to each subject.

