# TRIAL schedule

Visit 1 (Screening visit): -16 to -4 weeks

The following data will be obtained/checked and documented:

- Patient information and informed consent
- Age
- Gender
- Medical history and concomitant medications
- In- and exclusion criteria
- Best corrected distance visual acuity (ETDRS charts)
- IOP (GAT) (schedule to return for all visits at the same time (± 1 hour) as Visit 1.
- Slitlamp examination (biomicroscopy)
- Grading of conjunctiva (ORA redness scale)
- Photography (conjunctiva)
- Non-contact pachymetry
- Symptom survey / Questionnaires
- Urine pregnancy test if the patient is a woman of childbearing potential
- Patient instruction: patients have to discontinue their current glaucoma medication(s), starting 28 days prior to surgery
- Randomisation
- Dispense of medication, explanation of application
- Dispense of follow-up booklet
- Schedule the patient to return for the next visit, according to date of planned surgery

Visit 2: Day -1

- Changes in medical health and/or concomitant medication
- Adverse events
- Last day of administration of study drugs
- Collection of study medication after last dose
- Checking compliance
- Symptom survey / Questionnaires
- Best corrected distance visual acuity (ETDRS charts)
- IOP (GAT) at the same time as Visit 1 (± 1h)
- Non-contact pachymetry
- Optical coherence tomography
- Axial length (IOL Master)
- Anterior chamber depth (AC or IOL Master)
- Slitlamp examination (biomicroscopy)
- Grading of conjunctiva (ORA redness scale)
- Photography (conjunctiva)
- Schedule the patient to return for the next visit

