**Visit 5 (Final visit): Week 12 ± 7 days**

- Changes in medical health and/or concomitant medication
- Adverse events
- Symptom survey / Questionnaires
- Best corrected distance visual acuity (ETDRS charts)
- IOP (GAT) at the same time as Visit 1 (± 1h)
- Non-contact pachymetry
- Slitlamp examination (biomicroscopy)
- Filtration bleb classification (Grehn)
- Photography (conjunctiva)
- Optical coherence tomography
- Previous 5-FU injections and suture lyses
- Previous needlings
- Schedule the patient to return for the next visit

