#### Period of observation and Follow-up

In this trial, the period of observation for collection of adverse events extends from the time the subject has signed the informed consent document up to Visit 6.

All subjects who have adverse events, whether considered associated with the use of the investigational products or not, must be monitored to determine the outcome. The clinical course of the adverse event will be followed up according to accepted standards of medical practice, even after the end of the period of observation, until a satisfactory explanation is found or the investigator considers it medically justifiable to terminate follow-up, but no longer than 30 days after the end of the trial.

Should the adverse event result in death, a full pathologist’s report should be supplied, if possible.

If the investigator detects a serious adverse event in a trial subject after the end of the period of observation, and considers the event possibly related to the prior trial, he should contact the sponsor to determine how the adverse event should be documented and reported.

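### The pregnancy reporting rule is triggered by diagnosis during the four weeks of treatment, not by exposure, so an exposed pregnancy recognised after surgery carries no immediate-reporting duty

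*Protocol*

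**What the plan says.** Section 6.2.1.5 of the protocol (Immediate reporting by investigator) contains its only pregnancy-reporting rule: "any pregnancy diagnosed in a female subject or in the female partner of a male subject during treatment with the investigational product must be reported". The report goes immediately to the sponsor, on the SAE form.

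The length of treatment is given in several places. Section 4.1 states "Both treatment phases have duration of four weeks". The test regimen begins "28 days preoperatively (± 3 days): Discontinuation of all local antiglaucomatous drugs and IOP regulation with COSOPT-S", and the reference regimen starts in the same window. The trial schedule (section 5) marks Visit 2, Day -1, as "Last day of administration of study drugs". Section 4.1 also contains a sentence that does not fit with these: "Treatment with study medication will be discontinued at the end of the study".

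Other provisions run longer than treatment. The AE observation period in section 6.2.1.3 "extends from the time the subject has signed the informed consent document up to Visit 6". Contraception is required of women of childbearing potential for the trial, not only for the dosing period (section 3.6.1).

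Two provisions do not extend past dosing. The pregnancy item among the withdrawal criteria (section 3.6.3) reads "For women, if it becomes known that the subject is pregnant before Visit 2". The only scheduled pregnancy test is at Visit 1, before randomisation.

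**The concern.** A pregnancy-reporting rule in a drug trial serves to identify fetal exposure to study drug so that the outcome can be followed. What matters for that purpose is whether the pregnancy overlapped with dosing. The date on which someone notices it is a different matter, and here the rule depends on that date.

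In a trial with long treatment the two dates usually fall in the same period. Here dosing lasts four weeks and ends the day before surgery, so a pregnancy that begins on study drug may well be recognised only afterwards. The investigator is still seeing the subject at Day 7, Day 28 and Week 12, and perhaps at Week 24, yet the sentence as written asks for no immediate report.

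At stake is safety information on acetazolamide, dorzolamide, timolol or dexamethasone exposure in pregnancy, in female subjects and in partners of male subjects. Sample size, power and the primary analysis are not involved.

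**Working it through.** **1. The plan's own figure.** Start at Day -28 (± 3 days), last dose at Day -1, counted inclusively:

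- Nominal: -1 - (-28) + 1 = 28 days, which reproduces the stated four weeks.
- With the ± 3 day window: -1 - (-25) + 1 = 25 days, up to -1 - (-31) + 1 = 31 days.

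**2. Follow-up after the last dose.** Days after Day -1 = visit day + 1.

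- Visit 5, Week 12 ± 7 days: 84 + 1 = 85 days (78 to 92).
- Visit 6, Week 24 ± 14 days, optional: 168 + 1 = 169 days (155 to 183).

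With dosing ending at Visit 2, the pregnancy rule covers none of these days.

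**3. Share of on-drug conceptions recognised after the last dose.** The documents give no interval from conception to recognition, so the lag L is an assumption. With conceptions spread evenly over T dosing days, the share is min(L, T) / T.

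| Assumed lag L | T = 25 | T = 28 | T = 31 |
| --- | --- | --- | --- |
| 10 days | 10/25 = 40% | 10/28 = 36% | 10/31 = 32% |
| 14 days | 14/25 = 56% | 14/28 = 50% | 14/31 = 45% |
| 21 days | 21/25 = 84% | 21/28 = 75% | 21/31 = 68% |
| 28 days | 25/25 = 100% | 28/28 = 100% | 28/31 = 90% |

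The table leaves out pregnancies already present at first dose. Visit 1 may be 16 weeks before surgery, so the pregnancy test can precede the first dose by up to about 16 - 4 = 12 weeks. Pregnancies begun in that gap are exposed too. They are likelier to be recognised while dosing continues, and counting them would lower the share missed.

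**4. Do other provisions require a report?**

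- Section 6.2.1.1 counts new medical conditions and new diagnoses as possible AEs. Visits 3 to 6 ask about AEs and changes in medical health, and section 6.2.1.4 requires AEs on the CRF. A female subject's pregnancy could be recorded this way, but no text says that it must be, and the route is not immediate.
- A birth defect is a seriousness criterion. It captures one adverse outcome, not the pregnancy.
- Section 6.2.1.3 asks the investigator to contact the sponsor about a possibly related SAE found after the observation period. This too depends on an SAE.
- AEs are defined for trial subjects, so the partner of a male subject has no route other than section 6.2.1.5.

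**5. Expected number.** The documents do not say how many subjects or partners could become pregnant. An expected count of one would need 1/60 = 1.7% of all enrolled subjects to contribute an exposed pregnancy within about four weeks, although section 3.6.1 requires a negative test and contraception in women of childbearing potential. A value below one is a judgement, not a calculation.

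**The case against.** The strongest case against raising this is that it hardly matters here. Women of childbearing potential need contraception and a negative test, pregnancy is an exclusion criterion, all products have been in use for years, and probably no case will occur among 60 patients. That limits the weight of the point. It does not make the sentence do what it is for.

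The sentence could also be read so that the treatment period qualifies the pregnancy and not its diagnosis. That is possible but not the natural reading, and a duty to report within hours should not rest on it. Nor does the rule contain the word only; but no other pregnancy-reporting rule appears in the protocol. Section 6.2.1.6 leaves SAE workflow to a safety manual that is not at hand and may say more.

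The sentence that places the end of study medication at the end of the study would, taken literally, stretch the reporting period. It conflicts with the four weeks and with Visit 2 as the last dosing day, so it cannot be relied on to close the gap.

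Three stronger conclusions are tempting, and the documents do not support them:

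- **That nothing else would capture such a pregnancy.** For female subjects there is an optional AE route, and a birth defect would be an SAE.
- **That the rule misses most exposed pregnancies.** This depends wholly on the assumed lag: 36% at 10 days and exactly half at 14 days for 28 days of dosing, before counting pregnancies present at first dose.
- **That the sponsor would be unable to follow the outcome.** Nothing forbids a report or follow-up; the protocol simply does not require either.

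**Conclusion.** The point holds as a gap in a safety rule. Section 6.2.1.5 ties immediate pregnancy reporting to diagnosis during treatment, so a pregnancy exposed to study drug but recognised at Visits 3 to 6 carries no such duty, although AEs are collected to Visit 6. The gap is widest for partners of male subjects.

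The conclusion rests on the schedule in which dosing ends at Visit 2. The share affected is known only under an assumed recognition lag: from about a third at the shortest lag shown to all on-drug conceptions at 28 days, for 28 days of dosing. In this trial the practical effect is small, with an expected count probably below one, and no efficacy result changes. It is a minor but worthwhile correction.

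**What to change.** Reword the sentence in section 6.2.1.5 along these lines: *Any pregnancy in a female subject, or in the female partner of a male subject, that existed or began between the first and the last dose of study drug is reported to the sponsor immediately on the SAE form, whenever it becomes known up to the subject's last trial visit (Visit 6, or Visit 5 if the optional Visit 6 is not held). Its outcome is reported as follow-up on the same form.*

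The cut-off has to name both visits because Visit 6 is optional and section 5 heads the earlier one "Visit 5 (Final visit): Week 12 ± 7 days". Section 6.2.1.3 limits AE follow-up to 30 days after the end of the trial, so the new text should say whether that limit applies to pregnancy outcomes.

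Separately, reconcile the statements in section 4.1 and section 5 on when study medication stops, since the first and last dose define exposure under the new rule.

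The cost is two sentences in the protocol, and a matching line in the safety manual if it repeats the present rule. No visit or test is added; an outcome report may need one contact after the last visit.

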#### Safety evaluation by sponsor

According to GCP the sponsor is responsible for the continuous safety evaluation of the investigational product(s) and the clinical trial.

The sponsor or his delegate will conduct the management of SAEs and the expedited reporting as required by German Drug Law (AMG) and GCP regulation (GCP-V). Suspected unexpected serious adverse reactions (SUSARs) and safety issues as defined by GCP-V are determined for expedited reporting: The competent authorities and the ethics committees should be notified as soon as possible but not later than 15 calendar days if the event is non-fatal and 7 calendar days if it was fatal. All investigators and the marketing authorization holder of the IMP should be informed too.

Work flow and procedures concerning SAE management will be described in a safety manual.

During a clinical trial the sponsor or his delegate will submit the annual safety report including a list of all serious adverse (drug) reactions to the ethics committee(s) and the competent authorities once a year.

#### Emergency procedures

During and following a subject’s participation in the trial, the investigator should ensure that adequate medical care is provided to a subject for any AEs including clinically significant laboratory values. The investigator should inform a subject when medical care is needed for intercurrent illness(es) of which the investigator becomes aware.

## Other assessments

### Prior and concomitant illnesses

Relevant additional illnesses present at the time of informed consent are regarded as concomitant illnesses and will be documented on the appropriate pages of the case report form (CRF).

### Prior and concomitant treatments

Relevant additional treatments administered to the subjects on entry to the trial or at any time during the trial are regarded as concomitant treatments und must be documented on the appropriate pages of the CRF. Potassium replacement might be necessary in the reference group.

# Statistics

Details of the statistical analysis of the data collected in this trial will be documented in a Statistical Analysis Plan (SAP) that will be generated by IZKS Mainz and finalized before closing the data base. The SAP is based on the protocol including all amendments. The document may modify the plans outlined in this protocol; however any major modifications of the primary endpoint definition and/or its analysis will also be reflected in a protocol amendment. Any deviation from the original statistical plan must be described and justified in the final report. The statistical analysis will be conducted by means of SAS®.

## Sample size

Estimation of sample size was based on planning a non-inferiority test for the primary efficacy criterion, i.e. the change in IOP between baseline and month 3 after the OP. A difference of 4 mm Hg between both treatment groups regarding change in IOP is considered as the limit of clinical relevance (“Delta value”).

Analysis of a pilot study including seven patients treated with Cosopt-S® and three patients under standard treatment resulted in a common standard deviation of 3.7 mm Hg for both treatment groups. Taking into account uncertainties due to the small sample size of the pilot study, it is advised to base sample size estimation on a standard deviation of 5 mm Hg.

Application of the t-test model with  = 0.025 and  = 0.20 results in 26 evaluable patients per treatment group. Considering the fact that a bit more than 10% of patients may be non-evaluable for non-inferiority, a total of 60 subjects are planned to be included in the study.

## Analysis populations

All subjects who signed informed consent are considered as enrolled subjects.

All subjects who signed informed consent and were assigned a randomisation number are considered as randomised subjects, even if they did not receive any trial treatment.

To be eligible for the per protocol population, subjects must fulfil the following criteria:

- Treatment compliance of at least 8 days.
- No concomitant treatment with medication affecting IOP (steroids, glaucoma medication)

besides the study medication.

The safety population comprises all subjects who received at least one dose of trial treatment. In analyses of the safety population subjects will be assigned to the treatment which they actually received.

The analysis populations will be defined prior to locking the database.

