### Treatment after the end of the trial

After trabeculectomy, patients receive standard postoperative treatment. IOP lowering eye drops are usually not necessary.

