## Not permitted medication

The following concomitant treatments are not permitted during the trial:

- - Use of any systemic medication that would affect IOP with less than a 1-month stable dosing regimen before the screening visit (i.e. steroids).
  - Use of any additional local treatment that affects IOP (except topical steroids to prevent excessive scarring).

If the subject achieves prohibited treatment, exclusion of the trial will be discussed.

Concomitant topical therapy of the non-study eye will not be documented postoperatively.

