### Definition and analysis of primary endpoint

Change in IOP between baseline and three months post-OP was defined as the primary efficacy variable. A non-inferiority test will be carried out with to show that treatment with Cosopt-S® is not inferior to the standard preoperative treatment. An ANCOVA model will be implied including the IOP baseline value as a covariate. Δ = 4 mm Hg is specified as the non-inferiority limit. The significance level  is fixed at 0.025 to account for the one-sided testing situation. The primary analysis will be done for the per protocol population. The analysis will be repeated for the ITT population. Additionally, the 95% confidence interval for treatment differences will be displayed to check and to visualize the non-inferiority test results.

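### The per-protocol medication criterion has no time window, so as written it removes eyes on permitted topical steroids and eyes medicated after failed surgery from the primary non-inferiority analysis

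*Protocol*

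**What the plan says.** Section 7.3.1 fixes the primary analysis set: "The primary analysis will be done for the per protocol population". An ITT repeat follows. Section 7.2 sets two conditions for the per-protocol set, a minimum treatment compliance and "No concomitant treatment with medication affecting IOP (steroids, glaucoma medication") "besides the study medication". No period is attached to the second condition.

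Four other places determine how far it reaches:

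- Section 6.3.2: "Relevant additional treatments administered to the subjects on entry to the trial or at any time during the trial are regarded as concomitant treatments".
- Section 5, Visit 2 (Day -1): "Last day of administration of study drugs". The primary endpoint is measured at Visit 5, week 12.
- Section 4.2 lists as not permitted during the trial "Use of any additional local treatment that affects IOP (except topical steroids to prevent excessive scarring"). The exception names no period.
- Section 4.1.6: "After trabeculectomy, patients receive standard postoperative treatment", and "IOP lowering eye drops are usually not necessary".

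**The concern.** Two consequences follow from the wording.

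First, sections 4.2 and 7.2 disagree. A subject given topical steroids under the exception in 4.2 has been treated as the protocol allows, yet fails the steroid condition in 7.2. The exemption for study medication does not help, because study drug stops the day before surgery.

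Second, the rule selects on the outcome. Since drops are described as usually unnecessary after surgery, the eyes that receive them will mainly be those whose pressure is not controlled. Removing them takes high Visit 5 pressures out of the primary comparison. If the test regimen leads to more such eyes, more are removed from the test arm, the observed difference shrinks, and the bias runs towards declaring non-inferiority.

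Only failures treated with drugs are lost. Eyes managed by needling, 5-FU or reoperation alone remain in the set.

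**Working it through.** **Reach of the rule.** Section 7.2 bars concomitant steroids and glaucoma medication, 6.3.2 extends concomitant to the whole trial, and section 5 ends study drug on Day -1. From Day 0 to Visit 5 every steroid or glaucoma drug therefore counts against the subject, whether or not section 4.2 permits it.

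**The plan's own sample size.** Inputs from sections 7.1 and 3.2: margin 4 mm Hg, SD 5 mm Hg, one-sided alpha 0.025, power 80%, 30 per arm.

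- Normal approximation: n = 2 x 5² x (1.960 + 0.842)² / 4² = 24.5, so 25 per arm.
- Exact noncentral t, with noncentrality 4 / (5 x sqrt(2/n)): 79.1% at n = 25 and 80.7% at n = 26. The stated 26 per arm is reproduced.
- Allowance: 60 - 2 x 26 = 8 patients, or 13.3%.

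**Loss of power if eyes are excluded at random.** The same formula, starting from 30 per arm:

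| Share excluded | n per arm | Power | Enrolment needed for 52 evaluable |
|---|---|---|---|
| 13.3% | 26 | 80.7% | 60 |
| 20% | 24 | 77.4% | 52/0.8 = 65 |
| 30% | 21 | 71.6% | 52/0.7 = 74.3, so 75 |
| 50% | 15 | 56.2% | 52/0.5 = 104 |

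**Bias if the excluded eyes are those with high pressure.** None of the following inputs is in the documents except the SD, the margin and the arm size. Assume equal baselines, reference-arm Visit 5 pressure with mean 12 or 14 mm Hg, SD 5, the test arm truly 4 mm Hg higher (exactly the margin), and drops given above 18 or 21 mm Hg. The share above a threshold is 1 - Φ((threshold - mean)/5); for example, with mean 12 and threshold 18 it is 1 - Φ(1.2) = 11.5% in the reference arm and 1 - Φ(0.4) = 34.5% in the test arm. Non-inferiority is declared when the mean difference + t(0.975, df) x pooled SD x sqrt(1/n1 + 1/n2) is below 4. Simulation, 100,000 trials per row, 30 per arm before exclusion:

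| Reference mean / threshold | Eyes above, reference / test | Mean difference, all such eyes excluded | False non-inferiority, all excluded | Half excluded | No eye excluded |
|---|---|---|---|---|---|
| 12 / 18 | 11.5% / 34.5% | 2.3 | 30% | 7% | 2.5% |
| 12 / 21 | 3.6% / 15.9% | 3.0 | 13% | 5% | 2.5% |
| 14 / 18 | 21.2% / 50.0% | 1.8 | 43% | 6% | 2.5% |
| 14 / 21 | 8.1% / 27.4% | 2.5 | 24% | 7% | 2.6% |

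**Would simply keeping these eyes be enough?** The 2.5% column uses pressures without added drops. If the eyes stay in but are analysed at the pressure measured on drops, and the drops lower it by 4, 6 or 8 mm Hg (assumed), the same four settings give false non-inferiority of 6-22%, 10-49% and 14-75%. Retention alone does not restore the error rate.

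**The case against.** The strongest reply is that the condition was meant for the four-week preoperative phase. It sits beside a compliance rule about study drug and speaks of treatment alongside study medication. That may be the intention, and section 7.2 says the populations will be defined before database lock. But section 7.2 does not state the limit and section 6.3.2 points the other way. The trial is also open-label, so a window chosen late would be chosen by people who know the allocation.

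A second reply is that section 4.2 itself disallows additional local pressure-affecting treatment, so restarted drops are a deviation and a per-protocol set normally drops deviators. That is fair as convention. It does not remove the selection, because here the deviation is caused by the endpoint.

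A third is the ITT repeat. It would expose a gap between the two analyses, so it is a partial safeguard. It is not the primary test, section 7.2 does not define the set, and pressures measured on added drops would mask failure there too.

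The steroid exception in 4.2 might be read as meaning the reference arm's dexamethasone. That drug is study medication, though, and 4.2 concerns additional treatment.

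A reader might go further and infer that the per-protocol set would be nearly empty, either because every operated eye receives steroids or because 6.3.2 also counts treatment on entry and all patients enter after glaucoma therapy. The documents do not support this. They never say how many eyes receive postoperative steroids, and a rule excluding everyone for the therapy required at entry cannot be what was meant. A reader might also build a far worse error rate. With failures in 40% of test and 7% of reference eyes, each 12 mm Hg higher, all medicated and all excluded, non-inferiority is declared in 82-96% of trials. Those rates are not in the documents, the excluded set has zero difference by construction, and the implied pooled SD of about 5.8-6.5 exceeds the planned 5.

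**Conclusion.** The point holds as a flaw in a rule that the protocol states, not as a detail left for later. Followed as written, the criterion contradicts the steroid exception in section 4.2 and conditions the primary analysis on a consequence of the endpoint.

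The number of eyes affected is unknown. Any loss beyond 8 of 60 takes power below plan. When the test arm is truly at the margin, the selective loss raised false non-inferiority above 2.5% in every setting tried: modestly (about 5-7%) if half the high-pressure eyes are excluded, and substantially (about 13-43%) if all are. These sizes rest on the assumed reference means and thresholds. The direction rests only on drops going mainly to high-pressure eyes and on more such eyes arising in the test arm.

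**What to change.** Amend section 7.2 so that the criterion covers medication affecting pressure in the study eye from the start of study drug to Visit 2.

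Reconcile sections 4.2, 6.3.2 and 7.2: state the period to which the steroid exception applies, and state that topical steroids used within that exception do not exclude a subject. State also that an eye given pressure-lowering medication after surgery stays in the per-protocol set, whatever its status as a deviation under 4.2.

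Prespecify, for both the per-protocol and the ITT analysis, how a Visit 5 pressure measured under such medication is handled, for example by a fixed unfavourable value or by a sensitivity analysis. Drug and dates need to be recorded for this.

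The cost is a short amendment and some extra analysis, with no added patients or visits planned. Retaining these eyes will make the SD somewhat larger, so the planned 5 mm Hg should be looked at again in that light.
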